# Ohnut Versus a Waitlist Control for the Self-management of Endometriosis-Associated Deep Dyspareunia: Protocol for a Pilot Randomized Controlled Trial

**DOI:** 10.2196/39834

**Published:** 2023-03-27

**Keywords:** endometriosis, dyspareunia, randomized controlled trial, self-management, pilot project, pilot study, women's health, pain, gynecology, gynecologist, sexual health, sexual medicine

## Abstract

**Background:**

Endometriosis-associated deep dyspareunia is associated with reduced sexual quality of life, lower self-esteem, and impaired sexual function.

**Objective:**

The primary objective is to assess the acceptability of a phallus length reducer (brand name: Ohnut [OhnutCo]), which is a buffer worn over the penis or a penetrating object to reduce endometriosis-associated deep dyspareunia, and the feasibility of a definitive randomized controlled trial (RCT). The secondary objective is to obtain estimates of the effectiveness of the buffer. An embedded substudy will explore the acceptability and the preliminary validity and reliability of a vaginal insert for the self-assessment of deep dyspareunia.

**Methods:**

Ours is an investigator-initiated, 2-arm RCT. We will recruit 40 patient participants with diagnosed endometriosis between the ages of 19 and 49 years, as well as their sexual partners. The participating couples will be randomized in a 1:1 ratio into the experimental arm or the waitlist control arm. The length of the study period will be 10 weeks, during which time all participants will record deep dyspareunia severity following each episode of sexual intercourse. In weeks 1 to 4, all patient participants will record deep dyspareunia severity at each sexual encounter. In weeks 5 to 10, participants in the experimental arm will use the buffer during vaginal penetration; participants in the waitlist control arm will continue engaging in vaginal penetration as usual. Participants will complete questionnaires for assessing measures of anxiety, depression, and sexual function at baseline, at 4 weeks, and at 10 weeks. In the substudy, patient participants will self-assess dyspareunia by using a vaginal insert on 2 occasions, at least 1 week apart. The primary outcomes—the acceptability and feasibility of the buffer—will be assessed with descriptive statistics, and the secondary outcome—phallus length reducer effectiveness—will be assessed by using an analysis of covariance–based approach. For the vaginal insert, we will assess acceptability, test-retest reliability, and convergent validity via correlation analyses comparing the use of the insert to clinical examination in terms of dyspareunia assessment outcomes.

**Results:**

Our pilot will provide initial data on the acceptability and effectiveness of the buffer and the feasibility of the study methodology. The results from our study are expected to be submitted for publication by the spring of 2023. As of September 2021, we have consented 31 couples into the study.

**Conclusions:**

Our study will provide preliminary evidence for the self-assessment and management of endometriosis-associated deep dyspareunia. The findings will inform the decision to proceed to a definitive RCT.

**Trial Registration:**

ClinicalTrials.gov NCT04370444; https://clinicaltrials.gov/ct2/show/NCT04370444

**International Registered Report Identifier (IRRID):**

DERR1-10.2196/39834

## Introduction

Endometriosis is the presence of endometrial-like glands and stromata that abnormally grow outside the uterus [1]. This disease affects approximately 1 in 10 women and can cause various types of pain, including dysmenorrhea; chronic pelvic pain; and deep dyspareunia, which is defined as pain with deep vaginal penetration [1,2]. Deep dyspareunia is often neglected due to its intimate nature and reservations among both patients and clinicians in discussing sexual health [3,4]. People with endometriosis and deep dyspareunia have been shown to have significantly reduced sexual quality of life [5], lower self-esteem [6], and impaired sexual function [7]. Qualitative research has shown that many people with deep dyspareunia feel guilty about their pain and often continue to engage in penetrative activity even when the pain is severe [6].

Endometriosis-associated deep dyspareunia is multifactorial and can result from the endometriotic lesions themselves and other factors, such as myofascial pelvic pain and central nervous system sensitization [1,2,8]. A subset of patients do not experience improvements in deep dyspareunia after standard care, such as hormonal or surgical interventions for endometriosis [7-11], indicating an important need for self-management approaches. One self-management option is a phallus length reducer (PLR; brand name: Ohnut [OhnutCo])—a buffer that is worn externally over the penis or a penetrating object to reduce the depth of penetration [9]. Conceptually, this should reduce deep dyspareunia by limiting contact with deep pelvic structures; however, this intervention has not been empirically tested.

The assessment of deep dyspareunia for clinical and research purposes is challenging; pelvic examination in the clinical context may not reliably reflect sexual activities, particularly for patients who have experienced trauma [12], while questionnaire-based measurement is limited by recall bias that may be exacerbated for patients who have become abstinent as a result of dyspareunia. A study that investigated superficial dyspareunia among people with vulvodynia found that the Tampon Test—a self-administered test involving the insertion and removal of a tampon—was reliable and demonstrated good construct validity [13]. The study showed 95% adherence, providing evidence that participants found the test to be an acceptable method of assessing superficial dyspareunia [13]. Similarly, the self-assessment of endometriosis-associated deep dyspareunia by using a vaginal insert may be an acceptable, ecologically valid approach to assessing this symptom.

In our pilot randomized controlled trial (RCT) protocol, the primary objective is to assess the acceptability of a PLR and the feasibility of a definitive RCT. The secondary objective is to obtain estimates of the effectiveness of the PLR, which will be compared to those of a waitlist control for reducing endometriosis-associated deep dyspareunia. An embedded substudy will explore the acceptability, reliability, and preliminary validity if a vaginal insert for the self-assessment of deep dyspareunia.

## Methods

### Trial Design

Our study is a pilot study of a parallel-group, 1:1 RCT of the PLR, which will be compared to a waitlist control. An embedded substudy will investigate the use of a vaginal insert (brand name: Soul Source Rigid Plastic Vaginal Dilator Size #P1 [Soul Source Therapeutic Devices Inc]) [14] for the self-assessment of deep dyspareunia.

This protocol was developed by using the SPIRIT (Standard Protocol Items: Recommendations for Interventional Trials) checklist [15], the CONSORT (Consolidated Standards of Reporting Trials) extension for randomized pilot and feasibility trials [16], and published guidance for the reporting of protocols of pilot and feasibility trials [17]. This protocol describes the study rationale, proposed methods, organization, and ethical considerations.

### Study Setting

The study is being conducted at a tertiary care center for endometriosis within a large urban center in western Canada. Our research team manages a prospective patient registry called *Endometriosis and Pelvic Pain Interdisciplinary Cohort* (EPPIC; ClinicalTrials.gov trial number: NCT02911090) [18]. Baseline data collected in EPPIC are derived from patient-reported questionnaires and clinician-reported data from clinic consultations. The variables that are included in this prospective registry have been described previously [18]. New or rereferral patients at the center are invited to participate in the registry and can consent to being contacted about further research. In our study, all procedures will be conducted by the participants at home.

### Eligibility Criteria

Eligible patient participants will be new or rereferred patients in EPPIC who attended a clinic visit between January 1, 2018, and December 31, 2020; those who consented to being contacted for future research; and those who have a history of surgically confirmed endometriosis. Details of the inclusion and exclusion criteria are listed in Textbox 1.

Inclusion and exclusion criteria for the patient participants and their partners.
**Patient participants**
Inclusion criteria19 to 49 years of ageBirth-assigned femaleMonogamous sexual relationshipSexually active or not currently sexually active due to deep dyspareuniaSelf-reported deep dyspareunia score of ≥4 (out of 10)Sexual partner who consents to participating in the studyWilling to engage in penetrative sex at least once during the duration of the studyExclusion criteriaSelf-reported superficial dyspareunia score of ≥4 (out of 10; this is a potentially confounding variable, as the phallus length reducer is not expected to affect introital pain)Severe anxiety or depression symptoms in the last 2 weeks (Generalized Anxiety Disorder-7 or Patient Health Questionnaire-9 score of ≥15)Confirmed “yes” to question “In the last 2 weeks, have you had intense fear/anxiety in anticipation of, during or as a result of vaginal intercourse?”Current use of a phallus length reducerInability to complete English-language questionnaires
**Partners**
Inclusion criteria19 years of age or olderAny sex and genderExclusion criteriaCurrent use of a phallus length reducerInability to complete English-language questionnaires

### Sample Size

A sample size for a pilot study is often recommended to be at least 12 per group [19]. Given potential dropout and the uncertainty around the variance in acceptability, we will aim to recruit 20 participants and their sexual partners per group (ie, 40 couples or 80 total study participants).

### Recruitment

Individuals will be selected from a list of potential participants and will be telephoned and emailed about the study by a study coordinator. Interested individuals will be asked a series of screening questions to confirm that they meet the eligibility criteria. An important inclusion criterion listed in Textbox 1 is that participants must have a self-reported deep dyspareunia score of ≥4 (out of 10). This criterion was established to exclude patients who may have undergone surgery or other interventions that reduced deep dyspareunia symptoms. If the inclusion criteria are met and no exclusions are identified, patient participants and their partners will be emailed the consent form to review. The study coordinator will then review the consent forms with both the patient participants and their partners in a second telephone call and address any questions that the patient participants or their partners may have. Participants will give their consent to participate electronically, using an e-consent form.

### Interventions

The PLR (brand name: Ohnut) is made of a Food and Drug Administration–approved body- and skin-safe polymer blend. The blend is a thermo-set material that does not contain bisphenol A, phthalates, and latex and can be used with either silicone lubrication or water-based lubrication [20]. The PLR is a buffer that is worn externally over the penis or a penetrating object to limit the depth of penetration.

The vaginal insert is made of polyurethane and is stable from −40 to 70 °C. It will be self-inserted by the patient participants to self-assess the tenderness of pelvic structures implicated in deep dyspareunia that are typically assessed by a clinician during a pelvic examination. This is a novel, off-label use of the device.

To support the use of the vaginal insert and PLR, the study team developed patient-centered study booklets, which include instructions for the use of each tool (Multimedia Appendix 1). The instructions were developed with a gynecologist specialized in the assessment of dyspareunia, a pelvic floor physiotherapist with expertise in guiding patients to use vaginal inserts, and a clinical psychologist with experience in coaching patients and their partners to integrate the PLR in penetration. A medical illustrator was engaged to create diagrams for guiding the use of the vaginal insert.

### Outcomes

#### Primary Outcomes

The primary outcomes are the acceptability of the PLR and the feasibility of study methods. Details of the specific outcomes are listed in Textbox 2.

Primary outcomes of the feasibility and acceptability of the phallus length reducer (PLR).
**Outcomes and explanations**
Response: the number of individuals who responded divided by the total number of individuals contactedRefusal: the number of individuals who refuse to participate divided by the number of individuals who respondedScreen fail: the number of individuals who did not meet the inclusion criteria divided by the number of individuals who respondedRecruitment rate: the number of participants enrolled divided by the length of the recruitment period (months)Retention: the number of participants who complete the study divided by the number of participants enrolledAdherence: the number of sexual events completed with the PLR divided by the total number of sexual events reportedPLR acceptability: a 34-item, built-for-purpose questionnaire (adapted from a previously published measure for assessing the acceptability of female condoms [21]), with a response scale ranging from 1 to 5, will be completed by participants in the experimental arm in week 10 (Multimedia Appendix 1)

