### Assignment of Interventions

The study coordinator will use a REDCap (Research Electronic Data Capture; Vanderbilt University) extension package called *randomization* to randomly assign consented participants in a 1:1 ratio to 1 of 2 study arms; the experimental PLR arm will receive the PLR, and the waitlist control arm will receive the PLR once the study has concluded. Both arms will receive the vaginal insert for the substudy.

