### Participant Timeline

Throughout the study, all participants will continue concurrent endometriosis treatments and treatments for other conditions as usual. At the start of the study, both arms will complete baseline demographic, psychological, and sexual function questionnaires. In weeks 1 to 4 of the study, patient participants in both arms will engage in sexual activity as usual and be asked to record a daily diary of all sexual events and the severity of deep dyspareunia (score: range 0-10). Psychological and sexual function questionnaires will be repeated at the end of week 4. In week 5, participants in the experimental arm will receive and begin to use the PLR. Participants in the waitlist control arm will not receive the PLR and will continue to record deep dyspareunia severity at each sexual encounter. At the end of week 10, all patient participants will repeat the psychological and sexual function questionnaires, and participants in the experimental arm will indicate the acceptability of the PLR. At the conclusion of the study period, participants in the waitlist control arm will receive the PLR.

For the substudy, during weeks 1 to 4, all patient participants will self-assess deep dyspareunia by using the vaginal insert on weeks 2 and 3 of their menstrual cycle or on another two occasions (1 week apart) in the absence of regular bleeding. At the end of week 4, all patient participants will indicate the acceptability of the vaginal insert. The participant timeline is depicted in Table 1.

**Table 1 table1:** Schedule of interventions and assessments.

Groups and activities					Weeks 1 to 4							Weeks 5 to 10		
					Start of study		Vaginal insert self-assessment		Midstudy questionnaire		Experimental period			End of study

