### Acceptability of the PLR and Vaginal Insert

For the PLR and vaginal insert, an overall acceptability index will be calculated by summing the acceptability questionnaire item responses and dividing the sum by the total possible score. The index will be characterized by using means and SDs, and individual items will be reported by using medians and IQRs. For the PLR, results that are stratified by participant type (patient or partner) will be reported.

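### PLR acceptability is rated only once, at week 10, so couples who withdraw after receiving the device have no scheduled rating and the index risks overstating acceptability

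*Protocol article*

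**What the plan says.** Textbox 2 of the protocol article (Primary Outcomes) lists PLR acceptability among the primary outcomes. The instrument is "a 34-item, built-for-purpose questionnaire", its items are answered from 1 to 5, and the form "will be completed by participants in the experimental arm in week 10". The Participant Timeline repeats this: at the end of week 10, "participants in the experimental arm will indicate the acceptability of the PLR". In Table 1 the PLR feedback form appears only at the end of study, for patients and partners of the PLR group. No form at withdrawal is described.

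In the section headed Acceptability of the PLR and Vaginal Insert, the scoring rule is that "an overall acceptability index will be calculated by summing the acceptability questionnaire item responses and dividing the sum by the total possible score". This score is summarised by mean and SD, single items by median and IQR, and results are split into patients and partners. No cut-off for acceptable is given.

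The Sample Size section sets 20 couples per group against a recommended minimum of 12, with the reason "Given potential dropout and the uncertainty around the variance in acceptability". It gives no dropout rate.

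**The concern.** Acceptability of the device is the first objective named, and the findings are meant to inform whether a definitive trial goes ahead. Withdrawal after trying the device may itself be a sign that the device was not acceptable. With one form at the end, the couples whose opinion may be least favourable are the ones with no planned opportunity to give it.

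The article foresees such losses. The Discussion names retention and adherence as possible problems and links them to demanding procedures, among which it describes six weeks of PLR use. It then lists ways in which the device itself could trouble either partner. If withdrawal and dislike go together, the mean index describes the couples who stayed and reads too high for the couples who were given the device.

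**Working it through.** The plan states no index value, threshold or dropout rate, so there is no figure to reproduce. The check has three parts.

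**1. Who has a scheduled form** (Textbox 2, Participant Timeline, Table 1)
- Withdraws in weeks 1 to 4: never had the PLR, no form, no opinion of the device to lose.
- Receives the PLR in week 5 and withdraws before week 10: has had the device, no scheduled form. This is the gap.
- Stops using the PLR but stays in the study: still due the form at week 10.
- Completes: due the form.

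**2. Whether other parts of the plan recover the missing view**
- *Retention* is completers divided by enrolled. As defined it covers both arms and all weeks. Even if split by arm, it would not separate losses before and after week 5, and it carries no rating.
- *Adherence* is PLR events divided by all reported events. Data Management has the diaries collected on completion of the study, so withdrawn couples may be absent here too.
- *Missing data*: the rule is pairwise exclusion below 5% missing and multiple imputation above. It stands in the vaginal insert section, though its opening words also appear as an unfinished sentence under Statistical Methods, so its reach is uncertain. If it applies, 4 of 20 forms missing is 20%, which calls for imputation. The imputed values are modelled on couples who answered, and do not correct loss that depends on unrecorded dislike.

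**3. Possible size**

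Assumptions, not in the article: completer index 0.75; index of those lost 0.40 to 0.50; 20% of couples lost after receiving the PLR.

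Overstatement = share lost × (completer index − index of those lost)
- Lost at 0.40: 0.20 × 0.35 = 0.07, so the mean over all recipients is 0.68.
- Lost at 0.50: 0.20 × 0.25 = 0.05, mean 0.70.
- Lost at 0.75: 0.20 × 0 = 0, no bias.
- Lost at 1.00: 0.20 × (−0.25) = −0.05, acceptability understated.
- Worst case, lost at the lowest possible index of 0.20: 0.20 × 0.55 = 0.11, mean 0.64.

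Range of the index, from 34 items scored 1 to 5 and divided by 34 × 5 = 170:
- lowest 34/170 = 0.20
- all neutral 102/170 = 0.60
- all fours 136/170 = 0.80
- highest 170/170 = 1.00

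Rescaled to run from 0 to 1, (index − 0.20)/0.80 turns 0.60 into 0.50 and 0.75 into 0.69.

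**The case against.** The best reply is that survivor bias is possible here but not shown. The text does not restrict the form to completers or current users, and does not forbid sending it to couples who left. Couples who give up the device but stay in follow-up are still asked. The Discussion ties attrition to the burden of procedures and recording rather than to dislike alone. Retention and adherence are reported beside the index, so some loss would be visible. All of this stands, and it makes the overstatement conditional. It does not supply a rating from couples who withdraw after week 5.

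Four stronger readings are tempting, and the document does not support them.
- *The 0.20 floor inflates the result.* The floor is real, but it is a fixed linear offset. With no threshold and no reading as a percentage, it changes how the figure is interpreted and adds no bias.
- *Skipped items are scored as zero.* The formula, "summing the acceptability questionnaire item responses and dividing the sum by the total possible score", does not say how unanswered items are treated. Zero scoring is not a stated rule.
- *Half the users are ignored because waitlist couples are not asked.* In fact "the waitlist control arm will receive the PLR once the study has concluded". They are not users within the trial, so asking the experimental arm is the natural design.
- *Loss could be 40%.* The fall from 20 to 12 per group is 40%, but 12 is a general pilot-study minimum and not an expected rate. Some loss will also occur before week 5 and cannot reflect experience with the device.

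**Conclusion.** The point holds as a conditional risk to a primary outcome. The schedule leaves couples who withdraw after receiving the PLR without a planned rating, and retention, adherence and imputation do not recover it. If dislike drives those withdrawals, the mean index is too high: by 0.05 to 0.07 under the assumptions of 20% loss after receipt and indices of 0.75 and 0.40 to 0.50. A reader might infer that the trial will overstate acceptability. The article does not support that, since both the amount of loss and its cause are unknown and the direction can reverse. This is a cheap improvement worth making, not a flaw that invalidates the outcome.

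**What to change.** 1. Send the existing patient and partner PLR forms at withdrawal to every couple who has received the PLR.
2. Add a sensitivity result over all couples who received the PLR, counting those with no form as non-accepting. Setting them to the lowest index, 0.20, gives a lower bound. Report patients and partners separately, as already planned.
3. Report separately the experimental couples lost in weeks 1 to 4, who never had the device, and do not count them as rejecting it.
4. Optionally, as an aid to reading, state the possible range of the index (0.20 to 1.00, neutral 0.60), or score it as (mean of answered items − 1)/4 after checking that all items point the same way.

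The cost is one extra contact with withdrawing couples, using forms that already exist, and a few lines of analysis. The Results section reports 31 couples recruited by September 2021. For couples who have already finished, only the sensitivity result, the separate count and the rescoring remain possible.
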